### Eligibility criteria

Eligibility criteria for TBI patients are listed below. Participants will be allocated into four equal blocks randomized into two groups using an online randomization list.

### Inclusion criteria

Patients: traumatic brain injury adults aged 18–65 years oldAdmission to neurocritical care unit with all type of TBI diagnosisGlasgow Coma scale 7–9TBI patients with vitamin D (25-hydroxy vitamin D3) levels lower than 20 ng/mlReceived informed consent from patient’s parents or family members prior to intervention

### Non-entry criteria

Patients with hypercalcemia (Ca > 10.8 mg/dl)TBI patients who are NPO more than 48 h or have started total parenteral nutrition (TPN)Severe and active bleedingPatients treated with inotropic and corticosteroid drugsPatients treated with therapeutic dose of any vitamins and minerals apart from the routine ICU protocolPatients with body mass index (BMI) > 40 kg/m^2^ and BMI < 17 kg/m^2^History of any disease such as autoimmune disorders, cancer, sepsis, infection, liver disorder, kidney disorder, diabetes, heart failure, and metabolic diseasesKnown pregnancy and lactationPatients who are transferred from other ICUs after > 1 week

### Exclusion criteria

Death before 7 days of TBI patientsRequest to stop the study by patients’ parents or family membersPatients treated with a different medication protocolIf items 1 to 5 of non-entry criteria are met

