### Study objectives and rationale

The primary goal of the present study is to investigate the effect of daily intake of high-dose vitamin D (cholecalciferol) supplements (100,000 IU) versus low-dose vitamin D supplements (1000 IU) on mortality rate and inflammatory markers through a double-blind, randomized, controlled clinical trial on TBI patients. According to previous observational studies, TBI patients with vitamin D deficiency had higher mortality rate and neuroinflammation in comparison with TBI patients with vitamin D sufficiency [15, 17]. Also, as vitamin D deficiency is highly prevalent in critically ill patients, rapid normalization of this deficiency may be beneficial to these patients [7, 19, 20]. For this reason, we hypothesized that rapid correction of vitamin D deficiency in TBI patients may improve inflammation and decrease mortality rate. This study will also evaluate seven secondary outcomes that may be influenced by vitamin D administration in neurocritical patients. In order to determine the effects of high-dose vitamin D intervention, (1) Glasgow Coma Scale (GCS), (2) time of final weaning, (3) time of discharge from ICU, (4) SOFA (Sequential Organ Failure Assessment) score, (5) APACHE II (Acute Physiology and Chronic Health Evaluation II) score, (6) delirium severity, and (7) parathyroid hormone (PTH) test will be assessed in the treatment group compared to the control group. The study participants will be recruited from adult wards at trauma referral hospitals namely Kamyab and Taleghani in Mashhad, Iran. This study is a phase II RCT, and it has started from August 2019 and will carry on for 5 months.

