### Study design and setting

We will include 74 TBI patients with epidural hemorrhage (EDH), subdural hemorrhage (SDH), and subarachnoid hemorrhage (SAH) as diagnosed according to computed tomography (CT) scan or magnetic resonance imaging (MRI) findings by the neurosurgeon. Patients will receive vitamin D (cholecalciferol) drop (100,000 IU) or 1000 IU identical control drop in a 1:1 ratio through random assignment method. Vitamin D drops are manufactured by Zahravi Company under good manufacturing practice (GMP). Each vial of vitamin D drop is produced to be dissolved completely in 1 ml of extra virgin olive oil (Familia Company), through a nasogastric tube (NGT) for 5 days in TBI patients. Both high-dose and low-dose drops will have the same bottle, flavor, and aroma to the blinded.

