### Proposed analysis

To determine the normal distribution of variables, the Kolmogorov-Smirnov test will be conducted. The analysis will be performed according to the intention-to-treat (ITT) test. We perfomed an independent t-test or the Mann-Whitney test for continuous variables and the chi-square or Fisher exact test for categorical variables. Repeated measure one-way analysis of variance (ANOVA) or multivariable covariance analysis (ANCOVA) will be conducted to examine differences in severity of brain injury score (GCS), APACHE II score, SOFA score, delirium score, and all variables at study baseline between the two groups. Kaplan-Meier test was conducted and compared with the use of the log-rank test for estimates of survival time. The *P* values less than 0.05 will be considered statistically significant.

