### Primary efficacy endpoint

The primary efficacy outcome for this trial will be assessed by comparing the changes in vitamin D levels and inflammatory markers (IL-6, monocyte chemoattractant protein-1 (MCP-1), and C-reactive protein (CRP)) between two groups. The rate of mortality in TBI patients until 28 days after admission (in ICU and regular ward) will be assessed in high- and low-dose vitamin D supplement groups. The impact of high dose versus low dose of vitamin D will be analyzed, with and without adjustment for age, sex, type of brain injury, and severity of injury. If the results differ after adjusting for the variables, the results of both analyses will be reported.

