## Discussion

In the present study, if vitamin D significantly reduces the rate of mortality and inflammation in TBI patients, it can potentially provide the background for larger and well-designed multicenter clinical trial studies to establish the effect of vitamin D supplementation on TBI patients. Furthermore, vitamin D treatment is inexpensive and safe with minimal side effects and also could have positive impacts on critically ill patients (such as decreased mortality rate and hospital length) according to previous studies [7, 13, 14, 23, 24]. Potential limitations of the proposed study are as follows: measurement of vitamin D3 concentration with the chemiluminescence test instead of the gold standard method (liquid chromatography-tandem mass spectrometry). Another limitation is TBI patients’ blood transfusion because of trauma and bleeding; some TBI patients may require blood transfusion during the study, which may affect the biochemistry outcomes. Albumin injection in hypoalbuminemia patients can affect the levels of serum albumin. Also, TBI patients may need to undergo other surgeries than brain surgery; thus, this factor could affect the study outcomes. For this reason, we will compare mortality rate and inflammatory cytokine levels in all participants (intervention and control) and separate patients with anemia and hypoalbuminemia in each group. If the rate of death or inflammation in patients with anemia and hypoalbuminemia is different from those in the case or control group, the results will be reported separately. Based on recent studies, we have considered the suggested vitamin D dose (100,000 IU/day for 5 days) by Han et al. [23], as it is shown to be safe and efficacious in critically ill patients. Therefore, we believe that the present study could elaborate the necessity of vitamin D treatment and its efficacy on TBI patients at ICU.

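### Death before 7 days is a post-entry exclusion criterion, which contradicts the 28-day mortality endpoint and the intention-to-treat analysis

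*Protocol article*

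**What the plan says.** All references are to the protocol article.

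- **Exclusion criteria** lists "Death before 7 days of TBI" patients. It stands beside a family's request to stop, a changed medication protocol, and later occurrence of the first five non-entry items. The conditions that bar entry have their own list, Non-entry criteria.
- **Study objectives and rationale** gives the primary goal as the effect of high versus low dose "on mortality rate and inflammatory markers through a double-blind, randomized, controlled clinical trial on TBI patients".
- **Primary efficacy endpoint** states: "The rate of mortality in TBI patients until 28 days after admission (in ICU and regular ward) will be assessed" in the two dose groups.
- **Proposed analysis** states: "The analysis will be performed according to the intention-to-treat (ITT) test". On survival it adds: "Kaplan-Meier test was conducted and compared with the use of the log-rank test for estimates of survival time".
- **Study design and setting** has the drops given "through a nasogastric tube (NGT) for 5 days in TBI patients". The Discussion gives the high dose as "100,000 IU/day for 5 days".
- **Study assessments** puts the first blood sample after baseline on day 7.

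Nothing in the article confines the early-death exclusion to the marker analyses, or says that excluded patients still count for mortality.

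**The concern.** A death in the first week is an instance of the event that the trial sets out to compare. A rule that excludes a patient because of that death removes part of the endpoint. It also leaves a comparison among early survivors only. Early survival is determined after randomisation and may depend on the dose, so the two sets of survivors are no longer comparable by design.

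The first week matters here because it is when the high dose is given, or largely given, and because the stated hypothesis is about rapid correction of deficiency. A harm or benefit that acts quickly would show first in the deaths that the rule takes out. The Discussion intends a favourable mortality result to support larger multicentre trials, so a distorted comparison would carry forward.

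**Working it through.** **Step 1. Does the rule act after entry?** The first five non-entry items already bar a patient at the start. Repeating them under Exclusion criteria makes sense only if that list covers events after entry. The other entries (death, request to stop, changed medication) are also events of that kind. So the rule removes enrolled patients.

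**Step 2. Does it overlap the endpoint?** The endpoint runs from admission to day 28 and the rule covers deaths before 7 days. The starting point of the 7 days is not defined:

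- From first dose: the 5-day course lies wholly inside the 7 days.
- From admission: the course lies wholly inside if dosing starts within 7 − 5 = 2 days of admission.
- From injury: part of the course can fall after day 7. The non-entry criteria bar transfers from other ICUs only after more than one week, so dosing can start some days after injury.

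Most or all of the course is therefore likely, but not certain, to fall in the excluded period.

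**Step 3. How much could it matter?** The article gives no expected mortality, event count or timing of deaths, so there is no mortality figure to reproduce. Its sample size is for IL-6. From the article: 74 patients, 37 per arm. Assumed: 28-day mortality *p* of 20%, 30% or 40%, and share *f* of deaths before day 7 of 30%, 50% or 70%.

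Deaths removed = 74 × *p* × *f*. Mortality reported after exclusion = *p*(1 − *f*) / (1 − *pf*).

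| *p* | *f* | Deaths among 74 | Removed | Reported mortality |
|---|---|---|---|---|
| 20% | 30% | 14.8 | 4.4 | 0.14/0.94 = 14.9% |
| 20% | 50% | 14.8 | 7.4 | 0.10/0.90 = 11.1% |
| 20% | 70% | 14.8 | 10.4 | 0.06/0.86 = 7.0% |
| 30% | 30% | 22.2 | 6.7 | 0.21/0.91 = 23.1% |
| 30% | 50% | 22.2 | 11.1 | 0.15/0.85 = 17.6% |
| 30% | 70% | 22.2 | 15.5 | 0.09/0.79 = 11.4% |
| 40% | 30% | 29.6 | 8.9 | 0.28/0.88 = 31.8% |
| 40% | 50% | 29.6 | 14.8 | 0.20/0.80 = 25.0% |
| 40% | 70% | 29.6 | 20.7 | 0.12/0.72 = 16.7% |

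**Step 4. What could it do to the comparison?** Three constructed cases, to show the direction of possible bias:

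- *Early harm hidden.* Low dose: 30% mortality, half of it early. High dose: early deaths doubled to 30%, later risk among survivors unchanged at 17.6%. All randomised: 0.30 + 0.70 × 0.176 = 42.4% versus 30%. After exclusion: 17.6% in both arms, a difference of zero. Over the grid above, the difference lost in this way runs from about 5 to 23 percentage points.
- *Harm reversed.* High dose 15% early plus 10% later; low dose 5% plus 15%. All randomised: 25% versus 20%. After exclusion: 0.10/0.85 = 11.8% versus 0.15/0.95 = 15.8%.
- *Benefit lost.* High dose 5% early plus 10% later; low dose 15% plus 10%. All randomised: 15% versus 25%. After exclusion: 0.10/0.95 = 10.5% versus 0.10/0.85 = 11.8%, so 10 points shrink to about 1.

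**The case against.** The strongest defence is that the exclusion list is a set of discontinuation rules. On that reading, patients who die early simply leave treatment and the day-7 and day-14 sampling, the dropout allowance in the IL-6 sample size absorbs them, and intention to treat governs mortality. Early deaths would then be counted. This is possible, but the article does not say so, and it gives no rule for which statement prevails. The contradiction stands, while the loss of deaths is what the criterion prescribes rather than something certain to happen.

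Three further points limit what can be claimed.

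- A reader might infer that every death during the 5-day course drops out. With the 7-day clock undefined, this is not established.
- A reader might infer that early deaths also vanish from safety reporting, so that a fatal harm could never come to light. No section says this. The Safety section provides calcium and vitamin D monitoring and daily clinical examination, and a CONSORT flow diagram is referred to (figure not shown). Any loss from safety reporting is an inference from exclusion.
- The numerical cases rest on assumed rates, and the arm-specific ones were chosen to show hiding and reversal. The Background figure of more than 20% concerns deaths linked to infections in trauma patients. It is not all-cause 28-day mortality in this population.

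**Conclusion.** The point holds as a contradiction in the text with a possible, unquantified bias. The early-death exclusion cannot be reconciled with a 28-day mortality endpoint under intention to treat. If it is applied to mortality, the comparison conditions on early survival, and the Kaplan-Meier curves leave out deaths from about the first week. Under the assumed ranges, about 4 to 21 deaths among 74 patients would be removed, and an early harm or benefit could be hidden or change sign. These figures show what is possible and do not predict what happened. The day-7 sampling schedule explains why a patient who died early has no marker value, but gives no reason to drop that death from a mortality endpoint. The matter needs settling before the mortality result is reported.

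**What to change.** Delete death before 7 days from the exclusion criteria, or state that it applies only to the day-7 and day-14 marker analyses and define when the 7 days start. State that every death of a randomised patient to day 28 counts in the assigned arm, both in the mortality rate and in the Kaplan-Meier and log-rank analysis. Report early deaths by arm, and report by arm how many marker values are missing because of death.

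The Trial status section says recruitment ended on December 21, 2019, so the change now belongs in the definition of the analysis population. Day-28 status must be obtained for anyone already removed, on any of the listed grounds. Twenty-eight days after the close of recruitment is January 18, 2020, before the expected end of trial procedures at the end of that month. Mortality to day 28 is already a planned outcome, so the cost is a short statement, some follow-up of removed patients, and an account of missing marker values.

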### Sample size

To calculate the sample size, in accordance with a previous study [7], interleukin 6 (IL-6) will be used as the main variable and the type 1 error is considered with an alpha of 0.05. We estimated 62 TBI patients with 80% power to detect an effect size of 0.5 for reduction of IL-6 between the intervention and control groups as calculated with the formula shown below. Considering 20% dropouts in this study, the total sample size is estimated to be 37 participants in each group as calculated in the below formula [7]:
$$ \frac{\left(Z1-\frac{\alpha }{2}+Z1-\beta \right)2\ \left(\delta 12+\delta 22\right)}{\left(\upmu 1-\upmu 2\right)2} $$

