### Study assessments

At the beginning of the trial, demographic information, anthropometric parameters (weight (bed scale, Balas Company), estimating height from ulna length), mid arm circumference (measured by tape at the mid-point between the tip of the shoulder and the tip of the elbow), fat-free mass and fat mass (bioelectrical impedance analysis s10, InBody Company), vitamin D3 status (25-hydroxy vitamin D3, chemiluminescence method), IL-6 (ELISA kit), MCP-1 (ELISA kit), quantitative CRP (ELISA kit), PTH (ELISA kit), Ca, APACHE II score, SOFA score, and delirium score will be measured and repeated on days 7 and 14 after intervention in groups A and B. All drugs will be ordered daily upon physician’s request during ICU stay and will be recorded. For adjusting the effect of energy on final outcomes, based on ESPEN guideline for all patients, 25 kcal/kg actual body weight energy is considered [21]. Moreover, the total kilocalories and macronutrient delivered by enteral feeding will be calculated daily for all the participants. Blood samples (5 ml) will be collected at baseline (ICU admission) and 7 and 14 days after intervention at 10:00 am. Blood sample will be taken from veins and centrifuged at room temperature, then stored at − 20 °C. Finally, the samples will immediately be transferred with the cold box to a freezer − 80 °C for future inflammatory cytokine measurements. All routine biochemistry, hematology, and urine tests, until day 14, will be measured after sampling in Kamyab Hospital Lab, Mashhad, Iran. Serum IL-6, MCP-1, and CRP levels will be analyzed in the baseline and days 7 and 14 at the Immunology Lab of Bu Ali Research Institute, Mashhad, Iran. In addition, in case of occurrence of infections (blood stream, the urinary tract, the gastrointestinal tract, wounds, and the lung), an internist specialist will take responsibility [22]. A summary of the schedule of registration, supplementation, and study evaluation is shown in Fig. 3.

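### Five non-entry criteria are reapplied as exclusions after randomisation, which conflicts with the stated intention-to-treat analysis and the 28-day mortality outcome

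*Protocol article*

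**What the plan says.** The protocol article has two lists. Non-entry criteria begins with "Patients with hypercalcemia (Ca > 10.8 mg/dl"), followed by patients who are "NPO more than 48 h or have started total parenteral nutrition (TPN"). Counting on through the run-together list, item 3 is severe bleeding, item 4 is inotropes and corticosteroids, and item 5 is therapeutic doses of vitamins or minerals outside routine ICU care. Item 6 is the BMI limit.

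The second list, Exclusion criteria, contains death before day 7, a family request to stop, treatment under another medication protocol, and finally the case where "items 1 to 5 of non-entry criteria are met".

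Proposed analysis states: "The analysis will be performed according to the intention-to-treat (ITT) test". Primary efficacy endpoint defines the marker outcome as "comparing the changes in vitamin D levels and inflammatory markers" between groups, and adds "The rate of mortality in TBI patients until 28 days after admission (in ICU and regular ward"). Study assessments schedules the sampling: "Blood samples (5 ml) will be collected at baseline (ICU admission) and 7 and 14 days after intervention". Safety names hypercalcemia as the main side effect of cholecalciferol.

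**The concern.** An entry criterion applied before randomisation affects both arms alike. The same criterion applied after randomisation can act differently in the two arms, because the event may be a consequence of treatment. Hypercalcemia is the clearest case, since the article itself ties it to the study drug and the arms receive 100,000 IU against 1000 IU. Feeding failure, bleeding, inotropes and corticosteroids may mark a worsening patient, and the trial's hypothesis is that high dose improves inflammation and survival. Under that hypothesis, how often these events occur may depend on the arm.

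If such patients leave the comparison, the remaining arms are no longer comparable by randomisation. A benefit could be diluted, a harm could be hidden, and a death by day 28 in an excluded patient might not be counted.

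**Working it through.** **1. When the list applies.** Early death and a family request to stop cannot be screening criteria, so Exclusion criteria operates after entry. As an entry rule, its last item would also be redundant, because items 1 to 5 already bar entry under Non-entry criteria.

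**2. Whether it only stops study drug.** Stopping the intervention is dealt with separately under Safety, and early death, in the same list, cannot mean stopping a drug. The natural reading is exclusion from the trial. No section says that these patients remain in follow-up or in the analysis.

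**3. The conflict.** Proposed analysis promises intention-to-treat without exception, and mortality is to be assessed to day 28 in ICU and ward. A rule that excludes randomised patients for later events cannot be followed together with either statement.

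**4. Hypothetical size for IL-6.** The plan gives no figure for this bias, so there is none to reproduce. The only borrowed input is the effect size of 0.5 under Sample size, used here as a scale in SD units. (Read as a standardised difference, 0.5 does not reproduce the plan's 62 patients: two-sided alpha 0.05 and 80% power need 63 per arm. That is a separate matter and nothing below rests on it.)

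Let p be the share excluded in an arm and k the excess of excluded over retained patients, in SD of the analysed IL-6 outcome. An arm's full mean is (1 − p)·r + p·(r + k) = r + p·k, where r is the retained mean, so r lies p·k below the full mean. Hence:

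observed difference = 0.5 − (p_control − p_high)·k

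The values of p and k are assumptions.

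| k (SD) | 5 points more controls excluded | 10 points more controls excluded |
|---|---|---|
| 0.5 | 0.5 − 0.05×0.5 = 0.475 (5% lower) | 0.5 − 0.10×0.5 = 0.45 (10% lower) |
| 1.0 | 0.5 − 0.05×1 = 0.45 (10% lower) | 0.5 − 0.10×1 = 0.40 (20% lower) |
| 1.5 | 0.5 − 0.05×1.5 = 0.425 (15% lower) | 0.5 − 0.10×1.5 = 0.35 (30% lower) |

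With equal exclusion the second term is zero. If more high-dose patients are excluded the sign reverses: at k = 1 the effect appears as 0.55 to 0.60 SD. The direction is therefore open.

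**5. Hypothetical size for mortality.** Assume no true effect, 20% mortality in both arms, and 50% mortality among those excluded.

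retained mortality = (0.20 − p×0.50)/(1 − p)

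- 20% of controls excluded: (0.20 − 0.10)/0.80 = 12.5%.
- 10% of high-dose patients excluded: (0.20 − 0.05)/0.90 = 16.7%.

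The 4.2-point difference against high dose is produced by exclusion alone. Excluding 20% from each arm gives 12.5% in both, which is equal but too low.

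**The case against.** The strongest reply is that the article never says in words that these patients leave the analysis set or lose follow-up. Intention-to-treat is stated without exception, and mortality follow-up runs to day 28. This stands as a limit on wording. A reader might infer that the patients are certainly dropped and their deaths go uncounted. The document supports only that this is the natural reading, and that it does not say which rule governs.

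Four other inferences go too far:

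- **That the objective promises an effect in all randomised patients.** It speaks of the effect of daily intake; only the intention-to-treat sentence carries the commitment.
- **That these exits make up the planned loss.** Sample size says "Considering 20% dropouts in this study, the total sample size is estimated to be 37 participants in each group" but does not define dropouts. They could equally be withdrawals, early deaths or missed samples.
- **That the bias has a known size or direction.** Nothing in the document shows unequal exclusion, and the excess values are invented for illustration.
- **That every listed event means deterioration.** The article does not say so, and prolonged fasting or corticosteroid use may have other reasons.

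None of this removes the conflict. Nor is it a detail that an article leaves to the full protocol or analysis plan, because the article states both rules.

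**Conclusion.** The point holds as a conflict between two stated rules. Non-entry items 1 to 5 and treatment under another medication protocol act as exclusions after randomisation, while the analysis is said to be by intention-to-treat with 28-day mortality as a primary outcome. The finding rests on reading Exclusion criteria as removal from the trial, which its separate heading and companion items support but no sentence states.

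Bias is plausible, most directly through hypercalcemia because of its link to the study drug. Its size and direction cannot be derived from the document. The figure of 0.45 to 0.40 SD in place of 0.5 SD is conditional on a 1 SD excess and on 5 to 10 points more exclusions in controls. With equal exclusion, the mean difference is unbiased under that model but applies to a selected population. The correction should be made.

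**What to change.** Reconcile Exclusion criteria with Proposed analysis:

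- Use items 1 to 5 of Non-entry criteria as entry criteria only.
- State that patients who meet any of them after randomisation, or who are treated under another medication protocol, stay in follow-up: day 7 and day 14 samples and scores where obtainable, and vital status at day 28.
- Analyse them in the arm assigned and report the events by arm.
- Give the analysis without these patients as a sensitivity analysis only.

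Whether study drug continues is a separate clinical decision and is not touched by this change. The early-death item in the same list also has to be squared with intention-to-treat; this wording does not resolve it.

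The cost is small, because the samples and the 28-day outcome are already scheduled. Marker variance may rise slightly as sicker patients stay in. Trial status reports that recruitment ended on December 21, 2019, with procedures due to finish by the end of January 2020. Some samples may therefore be unrecoverable, but the analysis set can still be corrected and vital status sought.
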